Zimbabwe is primed for this type of mobile intervention. In 2014, Zimbabwe reached about 25% of its 1.3 million VMMC target for 2018 [42]. Although some AE underreporting is possible [42], Zimbabwe’s VMMC program is safe with the national VMMC program’s AE rate of 0.35% [42]. Under the current VMMC Zimbabwe Ministry of Health and Child Care (MoHCC) standards, **1 million additional VMMCs in Zimbabwe will translate into** **more than 2** **million unnecessary follow-up visits.** As each VMMC client likely passes through reception, observation, and examination, **the healthcare workload and time lost for VMMC clients healing without complication is likely several times higher.** Moreover, VMMC staff are MoHCC employees who perform most VMMCs in outreach sites (tertiary clinics, schools, communities). Unnecessary follow-up in outreach sites results in additional days away from routine clinic duties, stretching human resources required for myriad other health needs. While healthcare is strained, mobile technology is advancing rapidly: in 2014 approximately 81% of Zimbabweans had a cell phone [43]. This setting with high, unnecessary in-person VMMC follow-up; healthcare worker shortages; and high cell coverage is ideal to test and evaluate a better, low-cost approach to minimizing the burden on both the healthcare system and VMMC clients.

[figure not shown]

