As a national VMMC implementing partner, the ZAZIC consortium, led by the University of Washington’s International Training and Education Center for Health (I-TECH) and local implementing partners, The University of Zimbabwe(UZ)-University of California San Francisco Collaborative Research Program, Zimbabwe Association of Church-related Hospitals (ZACH), and Zimbabwe Community Health Intervention Research Project (ZiCHIRe), works in partnership with the Zimbabwe MoHCC to implement VMMC services in 10 districts. ZAZIC’s program is highly productive and safe: between July 2015-June, 2016, ZAZIC conducted 47,905 MCs and 45,989 follow-up visits to find 151 AEs, an AE rate of 0.3%[44]. Adherence to follow-up visits, another indicator of program quality [45], was good. Over 95% of men attended both Day 2 and Day 7 follow-up; more than 30% also had a Day 42 visit to verify complete healing [46]. With such high follow-up visits, **even if 20% of men were reviewed on Days 2 and 7 for high sensitivity of AE detection, almost 74,000 in-person visits were unnecessary and could potentially be replaced with 2wT interactions between patients and providers** (Figure 1). ZAZIC continues to rapidly scale up. In ZAZIC’s largest urban district, Chitungwiza, we have reached only 14% of the intended 80% target for 2018 [44], indicating ZAZIC projected exponential increase over the coming 2 years. Greater efficiency would enable more VMMCs.

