**Objective 1: Determine if 2-way texting can safely reduce VMMC follow-up visits**

Approach: Un-blinded, prospective, non-inferiority, RCT in high-volume facilities providing VMMC. Two-way texting (**2wT**) will provide interactive, text-based follow-up. 2wT men healing without complication could decline in-person follow-up; those with suspected AEs will be referred to in-person care. We will compare the safety outcome of combined moderate or severe AE rate ≤ Day 14 post-VMMC and the workload outcome of average number of in-person follow-up visits between control and intervention arms.

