## Data collection:

**
[figure not shown]
**Sample size: For Objective 1, the RCT will apply hypothesis testing for non-inferiority to examine the outcome of interest: AE rate (moderate or severe) occurring ≤ Day 14. A non-inferiority trial is appropriate as we wish to test our assumption that 2wT with reduced in-person follow-up is as safe (not clinically nor statistically inferior) as routine VMMC [59, 60], but with additional advantages including efficiency and lower direct and indirect costs to providers and patients. The non-inferiority margin, based on statistical and clinical considerations, is the maximum difference between the rate of AEs ≤14 Days in control and 2wT arms where we would conclude that 2wT is not inferior to routine care. We set that margin to 1.6% which would create a non-inferiority cutoff of 2% AEs or less in 2wT. The AE proportion cutoff for 2wT non-inferiority was set at a conservative 2% AEs to match the lower bound of AE rates reported by previous rigorous studies [1-3] and because an AE rate of 2% is regarded as a global standard of VMMC safety [61, 62], including in Zimbabwe [42]. Including a possible 10% LTFU, 361 participants per arm provides 90% power at an alpha of 2.5% to detect AEs greater than the non-inferiority margin of 1.6% (Table 2). We would conclude that 2wT is not inferior if we can rule out an AE rate of greater than 2%.

DATA ANALYSIS:

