**For Objective 1**, the 2wT safety outcome of interest is cumulative AE rate (moderate or severe) ≤ Day 14. Incidence of AEs before Day 14 will be extracted from routine VMMC data for both 2wT and control. Incident AEs on Day 14 will be identified, classified, and graded for severity using routine MoHCC protocols [9] and recorded on routine VMMC AE forms. We will compare cumulative rates of any moderate or severe AE ≤ Day 14 between groups using Fisher’s exact test as the expected number of AEs is low. The rates will be calculated per arm as: (# moderate + severe AEs)/ (total # VMMC clients who attend/responded to 2, 7 or 14 Day follow-up visits or texts). Multivariate logistic regression models (any AE v none) will quantify the magnitude of difference, adjusting for any potential confounders. To determine follow-up visit reduction, we will compare the mean number of in-person visits for intervention and control using a t-test. A multivariate linear regression model will further quantify the effect of intervention on visit reduction, adjusting for potential confounders. Secondary outcomes include: AE rates on Day 14, texting response rate, time between 2wT AE text reporting and follow-up, severity of AEs. We will perform appropriate summaries of missing data and LTFU, testing for systematic differences in response by study arm. *We hypothesize that 1) 2wT is non-inferior to routine follow-up for patient safety and that 2) 2wT* *will reduce unnecessary follow-up over standard care.*

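### The only test named for the safety outcome, Fisher's exact test of equal rates, does not carry out the non-inferiority rule for which the trial was sized.

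*Protocol*

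**What the plan says.** Protocol section 3, Objective 1, describes the trial as "Un-blinded, prospective, non-inferiority, RCT in high-volume facilities providing VMMC".

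The sample size paragraph in section 4 (under Data collection) says that "the RCT will apply hypothesis testing for non-inferiority to examine the outcome of interest: AE rate (moderate or severe) occurring ≤ Day 14". It defines the margin on the difference scale: it "is the maximum difference between the rate of AEs ≤14 Days in control and 2wT arms" at which 2wT would still be called non-inferior. The value follows: "We set that margin to 1.6% which would create a non-inferiority cutoff of 2% AEs or less in 2wT". The same paragraph gives 361 per arm, 90% power, alpha 2.5% and 10% loss to follow-up. It closes with a decision rule in absolute terms: 2wT is non-inferior if a rate above 2% can be excluded.

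The analysis paragraph for Objective 1 names one test for this outcome: cumulative rates are compared "between groups using Fisher’s exact test as the expected number of AEs is low". A logistic regression of any AE against none is added to describe the size of the difference. The paragraph mentions neither the margin nor a confidence limit, whether for the difference or for the 2wT rate.

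**The concern.** A non-inferiority conclusion requires rejecting the hypothesis that the excess AE rate is 1.6 points or more. Fisher's exact test, as named, can only reject equality. A significant result does not show that the excess reaches the margin, and a non-significant result does not show that it is below it. With one or two AEs expected per arm, non-significance is the likely outcome over a wide range of true rates, including some that the protocol treats as unacceptable.

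This is the safety question on which a reduction of in-person follow-up would rest. If the analysis section is followed literally, the report will contain a p-value that does not bear on the stated hypothesis. The method that does bear on it would have to be chosen later, when a handful of events could decide the answer.

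**Working it through.** **Inputs.** Margin 1.6 points, alpha 2.5%, power 90%, 361 per arm and 10% loss (361 × 0.9 ≈ 325 evaluable), all from the sample size paragraph. The control rate is not stated in the readable text (Table 2 is not legible). I take 2% − 1.6% = 0.4% as an assumption. For comparison, section 2 cites "the national VMMC program’s AE rate of 0.35" per cent and, for the implementing programme, "45,989 follow-up visits to find 151 AEs, an AE rate of 0.3" per cent.

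**Step 1: the plan's own figure.** Non-inferiority formula with equal true rates, one-sided alpha 2.5%:

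n = (1.960 + 1.282)² × 2 × 0.004 × 0.996 / 0.016² = 327.04, so 328 per arm.

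328 × 1.10 = 360.8, so 361, which matches. (Dividing by 0.9 gives 365.) A superiority calculation for 0.4% against 2.0% at two-sided 5% and 90% power needs about 972 per arm. The 361 therefore comes from a margin-based calculation, not from a test of equality.

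**Step 2: how Fisher behaves.** I enumerated all pairs of binomial counts and summed the probability of a two-sided Fisher p ≥ 0.05, with control at 0.4%. The score column is the probability that a score test against the 1.6-point margin, at one-sided 2.5%, concludes non-inferiority.

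| True 2wT rate | Fisher non-significant, 361 / 325 per arm | Score test concludes non-inferiority, 361 / 325 |
|---|---|---|
| 0.4% | 99.8% / 99.9% | 69% / 57% |
| 1.0% | 95% / 96% | 21% / 17% |
| 2.0% (at the margin) | 62% / 68% | 1.8% / 1.6% |
| 3.0% | 26% / 33% | 0.1% / 0.1% |
| 4.0% | 8% / 11% | under 0.1% |
| 5.0% | 2% / 3% | under 0.1% |

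With control at 0.3% and 2wT at 2.0%, Fisher is non-significant in 55% (361) or 62% (325) of trials.

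**Step 3: in event counts.** Against 0, 1 or 2 control AEs, Fisher first reaches p < 0.05 at 6, 8 or 10 2wT AEs, at either sample size. With 361 per arm, the score test permits a non-inferiority conclusion only up to 1, 1 or 2 2wT AEs; with 325 per arm, up to 0, 1 or 1. As an example, 7 against 1 AEs with 325 per arm (2.2% against 0.3%) gives Fisher p = 0.069, while the Miettinen-Nurminen upper 95% limit for the excess is 4.1 points, over twice the margin.

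**Step 4: can another stated analysis fill the gap?** The logistic model gives an odds ratio, and nothing converts it to a risk difference or sets a limit for it. The absolute 2% rule needs an upper limit for the 2wT rate, which a between-group Fisher test does not give either.

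**The case against.** The strongest reply is that the protocol does not adopt the misreading. It commits to a non-inferiority hypothesis, fixes the margin and alpha, and writes a criterion based on excluding an excessive rate. It never calls Fisher the primary test. An interval method is often left to a statistical analysis plan, which is not shown here. On this view the ingredients are all present and only a technical detail is missing.

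Part of this stands. A reader might infer that a non-significant p-value will be reported as evidence of safety. No sentence says so, and the exclusion criterion points the other way, so the 62% to 68% is conditional on that misreading. A reader might also infer that Fisher would be non-significant almost whatever the truth. The table does not support that: non-significance falls to 8–11% at a true 4% and 2–3% at 5%.

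The appeal to a later plan does not stand. The protocol does not leave the method open. It names a test for this outcome and gives a reason for it, and that test addresses a different hypothesis from the one in the sample size paragraph.

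**Conclusion.** The plan is wrong as written. The sample size paragraph and the analysis paragraph do not match: the trial is sized for a 1.6-point non-inferiority rule, and the only named test of the safety outcome cannot apply it. The data to be collected can still answer Objective 1; the named test cannot.

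If non-significance were taken as the answer, the false-claim rate at the margin would be about two in three instead of 2.5%. These sizes assume a 0.4% control rate, 325 to 361 evaluable men per arm and a two-sided 5% Fisher test; a one-sided 2.5% version gives almost the same figures. The mismatch itself depends on none of these assumptions.

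Correcting the test also brings out a second problem. The stated 90% power rests on a normal approximation (89.8% at 325 per arm). With so few events, exact power of the score-based rule at 0.4% in both arms is about 57% (325 per arm) to 69% (361 per arm).

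**What to change.** In the analysis paragraph for Objective 1, replace the Fisher sentence with wording such as: *The safety conclusion rests on the two-sided 95% confidence interval for the risk difference (2wT minus control) in the proportion of men with at least one moderate or severe AE by Day 14, by a score method (for example Miettinen-Nurminen) or an exact method suited to rare events. Non-inferiority is concluded if the upper limit is below 1.6 percentage points. Fisher's exact test is descriptive only.*

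Three things should accompany it:

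- Say openly that the numerator changes from a count of AEs to men with any AE. The current rate formula would count a man with two AEs twice.
- In the sample size paragraph, state that the 1.6-point difference governs, or reconcile it with the absolute 2% rule. The two coincide only at a control rate of 0.4%: at 0.3% the difference rule corresponds to 1.9%.
- Restate the power with an exact calculation for the chosen method, and give the assumed control rate.

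The change is to wording and needs no new data, but it has a cost. At the present sample size the stated 90% cannot be kept under the score-based rule, and the sponsor should know this before adopting the text.

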Building upon these previous mHealth initiatives, we seek to implement a two-way texting (**2wT**) intervention that **combines automated and interactive text messaging to maintain safety while dramatically reducing the burden that in-person VMMC follow-up places on weak health systems.** Automated messaging during Days 1-14 after circumcision could track men who are healing without complication, enabling a conservative estimate of more than 80% of clients to avoid unnecessary in-person follow-up at post-operative Days 2, 7 and 42. When a patient responds to an automated prompt message in a way that flags a potential AE, interactive messaging with a nurse would encourage them to promptly seek in-person, follow-up care. 2wT would act as active but efficient surveillance, improving care. By combining automated messaging to screen out cases with no complications and interactive texting to identify potential AEs, this intervention could make the care pathway far more efficient, reducing the costs of VMMC care over time for both providers and patients. **Reduced in-person follow-up could also free these same healthcare workers to perform additional VMMC surgeries.**

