VMMC care procedures (2wT arm): We will conduct a prospective, un-blinded, randomized control trial (RCT) among VMMC clients in a 1:1 ratio of control to intervention. Study participants and clinic staff are not masked to treatment. For the 361 men randomized into the intervention arm, men in the 2wT will receive routine VMMC surgical care and counseling, including referral cards for emergencies. 2wT clients will receive automated daily texts from days 1-14 (Table 1 and Figure 3). It is free to receive call and texts; it costs $0.05 to send a SMS in Zimbabwe [58]. If they respond that they suspect no adverse event, no immediate follow-up action will be taken. If a 2wT VMMC client responds affirmatively to any daily text that he suspects an AE, a VMMC nurse will exchange modifiable, scripted texts with the client to determine the symptoms, frequency, and severity. Then, if deemed necessary, the client will be asked to return to clinic the following day or earlier if an emergency is suspected. AE management will adhere to MoHCC standard care. If 2wT patients do not respond to texts on Day 2 or Day 7, the same MoHCC tracing process will be activated, after which they will be considered LTFU. All study participants will be asked to come to the clinic for study-specific, Day 14 follow-up to review healing and verify adverse event reporting. Day 14 was chosen for verification because 95% of all AEs within the ZAZIC VMMC program are reported Day 14 or earlier [44], suggesting that most AEs have occurred by this time point. In a previous field study of AEs, the most common AEs of bleeding and infection were found a mean of 6.7 and 9.0 days, respectively, after VMMC [20], further supporting the 14 day period used in this and a previous study[13]. The Day 14 review will be conducted by routine VMMC providers according to MoHCC review guidelines. At Day 42, we will implement a brief text-based survey with 2wT clients to ascertain complete healing, providing stronger inferences at study completion.

[figure not shown]

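### The primary AE rate accepts a text reply in place of an examination, so a 2wT man who misses Day 14 can count as AE-free without being seen

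*Protocol*

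**What the plan says.** The Data Analysis text for Objective 1 (Protocol, under Data collection) fixes the safety rate per arm as the number of moderate plus severe AEs over the "total # VMMC clients who attend/responded to 2, 7 or 14 Day follow-up visits or texts". One qualifying contact is enough, and a text counts the same as a visit.

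The numerator has two sources, both in the same paragraph: "Incidence of AEs before Day 14 will be extracted from routine VMMC data for both 2wT and control", and "Incident AEs on Day 14 will be identified, classified, and graded for severity using routine MoHCC protocols", recorded on the routine AE forms. An AE is counted only if a clinic has recorded it. The comparison is by Fisher's exact test, followed by "Multivariate logistic regression models (any AE v none").

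Under Study Procedures (2wT arm), "If they respond that they suspect no adverse event, no immediate follow-up action will be taken". Section 2 describes the intervention as "enabling a conservative estimate of more than 80% of clients to avoid unnecessary in-person follow-up at post-operative Days 2, 7 and 42". For routine care in the same programme, Section 2 reports: "Over 95% of men attended both Day 2 and Day 7 follow-up".

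Several provisions limit the problem. All men are asked to attend Day 14, and willingness to do so is an inclusion criterion. Attenders receive a $5 airtime credit. In the 2wT arm, "If 2wT patients do not respond to texts on Day 2 or Day 7, the same MoHCC tracing process will be activated". Missing data and loss to follow-up are to be summarised and compared by arm.

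**The concern.** The trial asks whether removing examinations is safe, yet its primary formula reads the absence of an examination as the absence of an AE. That reading falls mostly on the arm from which examinations are removed. Section 3 gives verification of self-reports as the purpose of Day 14 in the intervention arm, but the formula lets an unverified self-report stand.

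Such men are not flagged as missing, because a reply has already placed them in the denominator. The planned missing-data summaries may therefore not show them. With about one AE expected per arm, a few unrecorded events could decide the result.

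A second, smaller fault is that the formula puts a count of AEs over a count of men. Fisher's test and the logistic model both need men with at least one AE.

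**Working it through.** **1. How a man enters the rate**

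| Man | Denominator | Numerator |
|---|---|---|
| 2wT, texts no AE on Day 2 or 7, misses Day 14, no other visit | counted | 0, never examined |
| 2wT, attends Day 14 | counted | AE recorded if found |
| Control, seen Days 2 and 7, misses Day 14 | counted | AE recorded if found by Day 7 or at an unscheduled visit |
| Control, seen Day 2 only | counted | examined once, then taken as AE-free |

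Day 14 is not traced: the control-arm paragraph rules out active follow-up then, and none is stated for 2wT. Study Procedures also treats a 2wT man who misses the Day 7 text and cannot be traced as lost to follow-up. The denominator keeps him if he answered on Day 2. The two passages disagree.

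**2. The plan's own sample size.** Inputs from the Sample size paragraph: margin 1.6 points, cutoff 2%, alpha 2.5% (taken as one-sided), power 90%, loss 10%. The implied control rate is 2.0% − 1.6% = 0.4%.

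n = (1.960 + 1.282)² × 2 × 0.004 × 0.996 / 0.016² = 327.04, so 328 per arm. Then 328 × 1.10 = 360.8, so 361, which is the stated figure. Evaluable men: 361 × 0.90 ≈ 325 per arm. Expected AEs per arm at 0.4%: 325 × 0.004 = 1.3.

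**3. Effect at the non-inferiority boundary.** Assumptions: the true 2wT rate is 2.0%, the control rate is 0.4% and fully recorded, a fraction u of the 2wT denominator is unexamined, and none of their AEs is recorded. The recorded 2wT rate is 2.0% × (1 − u). Non-inferiority is declared if the upper 97.5% bound of the difference is below 1.6 points. Probabilities come from exact binomial enumeration with 325 per arm. The paragraph names Fisher's test without saying how the margin enters, so two common bounds are shown.

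| u | Recorded 2wT rate | Difference (points) | False non-inferiority, score | False non-inferiority, Wald |
|---|---|---|---|---|
| 0% | 2.0% | 1.6 | 1.6% | 5.3% |
| 10% | 1.8% | 1.4 | 2.6% | 8.2% |
| 20% | 1.6% | 1.2 | 4.2% | 12.7% |
| 30% | 1.4% | 1.0 | 6.8% | 19.2% |
| 40% | 1.2% | 0.8 | 10.8% | 28.2% |

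If only half of those AEs go unrecorded, u = 20% gives 2.6% (score) or 8.2% (Wald). The range of u is an assumption, since the protocol gives no Day 14 attendance.

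**4. How few events decide.** With 325 per arm and one control AE, non-inferiority allows at most one 2wT AE (score) or two (Wald).

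**5. AEs counted instead of men.** If one 2wT man has two AEs, 1 v 1 becomes 2 v 1. The Miettinen-Nurminen upper limit moves from 1.44 points (passes) to 1.94 (fails). The Wald limit for 2 v 1 is 0.31 + 1.96 × 0.53 = 1.35 points, which still passes.

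**The case against.** The strongest reply is that the design already requests an in-person Day 14 check of every man, recruits only men willing to attend, pays a credit and traces missed Day 2 or Day 7 replies. A man with a single early text should therefore be traced at Day 7, and a man with symptoms is referred to clinic, where his AE enters the routine record. This stands as mitigation. At 10% unexamined, the loss the protocol itself allows for, the score-test error is 2.6%, barely above the nominal 2.5%. But none of these steps makes examination a condition of the denominator.

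Stronger readings are tempting, and the protocol does not support them:

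- **That the bias certainly favours 2wT.** Daily prompts to Day 14 may raise detection. Study Procedures cites mean detection at 6.7 days for bleeding and 9.0 days for infection, so controls examined on Days 2 and 7 who skip Day 14 could have later infections missed. The direction is expected, not proven.
- **That the control rate is not diluted.** A control man seen only early is also taken as AE-free to Day 14. Shared under-recording does not cancel in a risk difference, however: losing 20% of AEs in both arms turns 1.6 points into 1.6 × 0.8 = 1.28.
- **That Day 14 attendance will be about 60-65%.** Section 2 gives 59.7% and 65.4% for 7-day visits in another trial. This programme's own figure is over 95% at Days 2 and 7. Neither measures Day 14 attendance here.
- **That one double-counted man overturns the result.** That depends on the interval method, could happen in either arm, and is unlikely at 1.3 expected AEs per arm. The analyses named are already person-level, so only the formula needs correcting.

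**Conclusion.** The point holds as a fault in a stated primary-analysis rule. The formula accepts a text reply as evidence of AE-free status to Day 14, and the two arms reach the denominator by different routes.

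Under the stated assumptions the false non-inferiority risk by the score test passes the nominal 2.5% at about 10% unexamined and reaches 10.8% at 40%. With few unexamined men, or if most of their AEs reach the clinic record anyway, the effect is small. The mechanism is certain from the text. The direction is only expected, and the size cannot be fixed from the protocol. The mismatch between AEs and men is secondary.

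**What to change.** 1. Define the endpoint as men with at least one moderate or severe AE by Day 14, analysed by randomised arm, and correct the numerator to match.
2. Treat status as ascertained, identically in both arms, only with an in-person Day 14 examination or an earlier clinician-confirmed AE. A text reply alone is not ascertainment. Men without ascertained status are counted as missing and reported by arm.
3. Report the all-randomised analysis alongside. It should not be the sole remedy, because it takes every unexamined man as AE-free and so dilutes further. The ascertained set has the opposite weakness: early AE cases enter without a Day 14 visit, while unexamined men without an AE do not. The two should be read together.
4. Add a tipping-point table showing how many AEs among unexamined 2wT men would overturn non-inferiority.
5. Reconcile the loss-to-follow-up rule in Study Procedures with the denominator.

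The cost is wording and a little programming. The planned 361 per arm need not change, but the evaluable set will be somewhat smaller than the 328 required if Day 14 attendance is low.

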## Study Procedures:

Participant overview:

- 50 men for the pilot. Not randomized. Enrolled into texting. Not included in outcome analysis.
- 722 men in the full study randomized in a 1:1 ratio of texting and control for 361 men in texting and 361 in control (routine care).
- Same recruitment, consent, and follow-up procedures in pilot and intervention as outlined, per group, below

Recruitment and Informed Consent: Each site will establish local recruitment and screening methods that operationalize protocol-specified requirements for eligibility determination in a manner that is tailored to and most efficient for the local study setting and target study population. In brief, information about the study will be disseminated through the Zimbabwe Ministry of Health and Child Care (MoHCC), ZAZIC, and HCW at the selected sites. VMMC demand creation as part of routine ZAZIC program practice will support study recruitment. HCW recruited for participation in the study will be reached at their workplaces (the health care facilities) following communication between the study team and the site leadership. VMMC clients will be recruited in the VMMC clinic area. Recruitment will be managed by a specifically-trained research coordinator. This research coordinator will meet with VMMC patients to sensitize them about the opportunity to participate in a study of text-based follow-up; those meeting eligibility criteria will be individually informed by 2wT staff about the opportunity to participate in the study. Interested patients will be referred to the site study coordinator for study enrollment and informed consent. This person will meet with patients in a private setting, further explain the study, confirm study eligibility, and seek informed consent. Participants who refuse to enroll in the study will be asked to provide informed consent for data collection about reasons for non-participation.

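### The size of the AE difference is to come from a confounder-adjusted logistic model when about 2.6 events are expected; a risk difference with a score interval should take that role

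*Protocol*

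**What the plan says.** The protocol's sample size paragraph (section 4, Data collection) puts the safety question on the difference scale. The margin "is the maximum difference between the rate of AEs ≤14 Days in control and 2wT arms". Its value follows: "We set that margin to 1.6% which would create a non-inferiority cutoff of 2% AEs or less in 2wT". The size is justified by "361 participants per arm provides 90% power at an alpha of 2.5" per cent, with the allowance "Including a possible 10% LTFU". Allocation is "722 men in the full study randomized in a 1:1 ratio of texting and control for 361 men in texting and 361 in control".

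The analysis paragraph for Objective 1 then does three things for the safety outcome:

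- It defines a moderate or severe AE rate for each arm.
- It compares the arms with Fisher's exact test, giving the small number of expected AEs as the reason.
- It adds the model: "Multivariate logistic regression models (any AE v none) will quantify the magnitude of difference, adjusting for any potential confounders".

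It names no covariates, no method for sparse data and no step from an odds ratio to a difference in rates. It also states no confidence interval for that difference.

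**The concern.** The protocol recognises sparse data when it picks the test, then gives effect estimation to the type of model that sparse data defeat first. Beyond the crude rates and Fisher's test, this model is the only between-arm estimate of effect named for safety.

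If one arm has no events, an ordinary logistic fit gives an odds ratio of zero or infinity. If neither arm has any, there is no estimate at all. The trial is meant to support a decision on wider use, and it could finish without a usable figure for how much safety changed, or with an interval too wide to inform anyone. An open covariate list adds a further choice, to be made when the model is already struggling.

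**Working it through.** **Inputs.** Margin 1.6 points, cutoff 2%, 361 per arm, 90% power, alpha 2.5% and 10% loss all come from the sample size paragraph. The implied control rate is 2% − 1.6% = 0.4%; the text does not state it. I read the model's outcome as moderate or severe AE, in line with the stated endpoint.

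**Reproducing 361.** With the same rate p in both arms and one-sided alpha 2.5%:

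n = 2p(1−p)(z₀.₉₇₅ + z₀.₉₀)² / 0.016² = 2 × 0.004 × 0.996 × (1.960 + 1.282)² / 0.000256 ≈ 327.04, so 328.

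Adding 10%: 328 × 1.1 = 360.8, so 361. This matches the protocol. Rates of 0.3% and 0.35% would give 271 and 316 by the same route, so 0.4% is the planning rate.

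**Expected events.** Evaluable per arm: 361 × 0.9 ≈ 325. Total: 650 × 0.004 = 2.6. If all 722 are evaluable, 722 × 0.004 = 2.9. With 650 evaluable, the binomial chance of two or fewer events in the whole trial is 52%.

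**Chance of an empty arm.** P = 1 − [1 − (1−p)³²⁵]². At 0.4%, 0.996³²⁵ = 0.272, so P = 1 − 0.728² = 0.470. With 361 evaluable per arm it is 41.5%.

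| True rate, both arms | Source | Expected events | P(at least one arm has none) |
|---|---|---|---|
| 0.3% | Background: "ZAZIC conducted 47,905 MCs and 45,989 follow-up visits to find 151 AEs, an AE rate of 0.3" per cent | 1.95 | 61% |
| 0.35% | Background: "the national VMMC program’s AE rate of 0.35" per cent | 2.3 | 54% |
| 0.4% | implied planning rate | 2.6 | 47% |
| 0.8% | Background, regional average | 5.2 | 14% |
| 1% | assumption | 6.5 | 7% |
| 2% | the cutoff | 13 | 0.3% |

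With 0.4% in control and 2% under texting (7.8 events expected), P is 27%.

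**Adding covariates.** In 3,000 simulated trials per model at 0.4%, separation or no events at all occurred in 48% with arm alone, 59% with one balanced binary covariate, 67% with two, and 99% with indicators for five sites. The figures with covariates count a non-finite value for any coefficient, not only for arm.

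**Precision when the estimate is finite.** For one event in each arm, SE(log OR) = √(1/1 + 1/1 + 1/324 + 1/324) = 1.416. The OR is 1.0 with 95% CI exp(±1.96 × 1.416) = 0.06 to 16. For two in each arm it is 1.0 (0.14 to 7.1).

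**Scale.** The odds ratio that matches a 1.6-point difference is [(p+0.016)/(1−p−0.016)] / [p/(1−p)]. This is 6.4 at a control rate of 0.3%, 5.1 at 0.4%, 3.0 at 0.8% and 1.8 at 2%.

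**The alternative on the same data.** Newcombe's score interval combines the Wilson limits of each arm.

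- 0 v 0 events: the Wilson upper limit is 3.84/(325 + 3.84) = 1.17%, so the difference is 0 (−1.17 to 1.17 points).
- 1 v 1: Wilson limits are 0.054% and 1.722% around 0.308%. The half-width is √(1.414² + 0.253²) = 1.44 points.
- 2 v 2: Wilson limits are 0.169% and 2.216% around 0.615%. The half-width is √(1.600² + 0.446²) = 1.66 points.

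The interval exists in every case and can be read directly against 1.6 points.

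**The case against.** **The test does not depend on the model.** Fisher's exact test is the named comparison, and the per-arm rates give a crude difference without any regression. This stands. A reader might infer that the safety analysis as a whole collapses, or that nothing else conveys the size of the difference; the protocol supports neither.

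**The protocol never says the odds ratio will be judged against the margin.** This also stands. The decision rule is worded in AE rates. The scale point is therefore no contradiction. It means only that the one modelled estimate cannot be read against the margin without a control rate or a conversion, and neither is given.

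**The estimator and covariates could be settled in an analysis plan.** This stands in part. The protocol does not say maximum likelihood, and Firth or exact fits are also logistic regression. But the protocol itself gives an adjusted model the job of quantifying the difference, and the event count makes that a poor choice whatever details follow.

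**True rates may be higher.** The Background cites 0.5% to 8% in pilot studies and trials and concedes possible under-reporting, and this study adds a Day 14 examination. At 2% an empty arm is rare. Even so, 13 events support very little adjustment.

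**Bias.** A reader might infer that any finite odds ratio here is biased away from 1. That is wrong. In the arm-only model, finite log odds ratios average 0 when the arms are equal. At 0.4% v 2% they average 1.35 against a true 1.63, which is towards 1. The sound criticism is imprecision.

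**Conclusion.** The concern holds as a weakness in the planned effect estimate, not in the named test. At the protocol's own planning rate, about 2.6 events are expected and an ordinary fit gives no finite odds ratio for arm in 47% of trials before any covariate enters. Finite estimates are close to uninformative.

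This rests on the implied 0.4% rate (confirmed by reproducing 361), on about 325 evaluable men per arm, on an ordinary maximum-likelihood fit, and on the outcome being moderate or severe AEs. Counting mild AEs would add events. The failure rate is sensitive to the true AE rate, from 61% at 0.3% to 0.3% at 2%. Across that range the expected total is only about 2 to 13 events, too few for open-ended confounder adjustment. As arms are randomised, that adjustment is not needed for a valid comparison.

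**What to change.** In the analysis paragraph for Objective 1, replace the sentence on logistic regression with text to this effect: the difference in moderate or severe AE rates through Day 14 (2wT minus control) will be estimated as an unadjusted risk difference with a two-sided 95% score confidence interval, and the upper limit will be read against the 1.6-point margin. Any logistic model will be supportive only, fitted by a Firth-penalised or exact method, with arm and at most a very small prespecified covariate set. Name the score method. Keep covariate adjustment for the number of in-person visits, where every man contributes information.

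The change takes a sentence or two and needs no new data. It gives up adjusted odds ratios that the data could not support. It also makes the limits of the evidence visible: two events in each arm already put the Newcombe upper limit at 1.66 points, just beyond the margin.
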